### Adverse Events Management

We do not anticipate any adverse events for patients in this observational study.

### Data Management and Monitoring

Before the initiation of the study, an electronic case report form will be established with password-protected access. Each enrolled patient will be assigned an identification number. Patient data will be coded and kept confidential. We will indicate a coordinator to ensure the integrity of data collection and timely completion of the case report form. Trial conduct will be audited monthly by personnel independent of investigators with no competing interests.

### Statistical Analysis

A prior study that used EIT to assess ventilation distribution in patients undergoing major open abdominal surgery found that a two-sided significance level (α) of 0.05 and a target power of 80% would require 10 subjects (19). We aim to recruit 50 patients, surpassing the minimum necessary for our target power and significance level. Analyses will be conducted using SPSS 21.0 (IBM, Armonk, New York, USA). Continuous variables will be expressed as means (95% confidence intervals, CI) or as medians (interquartile range). Categorical variables will be analyzed using the chi-square test. Means or medians will be compared between groups using the *t*-test, the Mann-Whitney *U*-test, and one-way analysis of variance with F- or Kruskall-Wallis tests, when appropriate. Pearson correlation or Spearman rank correlation coefficient will be used to assess the correlation between variables, as appropriate. Intention-to-treat analyses will be carried out using mixed models. All tests will be 2-sided, and significance will be set at the 0.05 probability level.

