## Abstract

**Background:** Pulmonary complications are common in patients after upper abdominal surgery, resulting in poor clinical outcomes and increased costs of hospitalization. Enhanced Recovery After Surgery Guidelines strongly recommend early mobilization post-operatively; however, the quality of the evidence is poor, and indicators for quantifying the effectiveness of early mobilization are lacking. This study will evaluate the effectiveness of early mobilization in patients undergoing an upper abdominal surgery using electrical impedance tomography (EIT). Specifically, we will use EIT to assess and compare the lung ventilation distribution among various regions of interest (ROI) before and after mobilization in this patient population. Additionally, we will assess the temporal differences in the distribution of ventilation in various ROI during mobilization in an effort to develop personalized activity programs for this patient population.

**Methods:** In this prospective, single-center cohort study, we aim to recruit 50 patients after upper abdominal surgery between July 1, 2021 and June 30, 2022. This study will use EIT to quantify the ventilation distribution among different ROI. On post-operative day 1, the nurses will assist the patient to sit on the chair beside the bed. Patient's heart rate, blood pressure, oxygen saturation, respiratory rate, and ROI 1-4 will be recorded before the mobilization as baseline. These data will be recorded again at 15, 30, 60, 90, and 120 min after mobilization, and the changes in vital signs and ROI 1-4 values at each time point before and after mobilization will be compared.

**Ethics and Dissemination:** The study protocol has been approved by the Institutional Review Board of Liaocheng Cardiac Hospital (2020036). The trial is registered at chictr.org.cn with identifier ChiCTR2100042877, registered on January 31, 2021. The results of the study will be presented at relevant national and international conferences and submitted to international peer-reviewed journals. There are no plans to communicate results specifically to participants. Important protocol modifications, such as changes to eligibility criteria, outcomes, or analyses, will be communicated to all relevant parties (including investigators, Institutional Review Board, trial participants, trial registries, journals, and regulators) as needed via email or in-person communication.

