## Methods and Analysis

### Study Design

This prospective, single-center, single-cohort study will be conducted in the Surgical Intensive Care Unit (SICU) at the Liaocheng Cardiac Hospital in Shandong Province in China.

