### Procedure

Study procedures will be carried out in the following steps:

Once a patient meets inclusion criteria and provides a written informed consent, the following data will be collected: age, sex, weight, height, BMI, smoking history, type and duration of surgery, comorbidities, arterial blood gas analysis (PH, PaO_2_, PaCO_2_, FiO_2_), chest X-ray or computed tomography (CT), pain (11-point NRS), and the time from admission to the ICU to the first mobilization.The following baseline parameters will be recorded when the patient is in decubitus position (T_0_): heart rate (HR), blood pressure (BP), oxygen saturation (SO_2_), respiratory rate (RR), and EIT ROI 1-4. The duration of each EIT recording will be 2 min.The patient will be seated in a chair beside the bed with assistance. Oxygen therapy method and oxygen concentration will be the same as that before getting out of bed.The parameters presented in step 2 will be recorded at 15 min (T_1_), 30 min (T_2_), 60 min (T_3_), 90 min (T_4_), and 120 min (T_5_) for each patient after getting out of the bed.

After patients reach the 120-min time point, their participation in the study will be complete. No further interaction with the enrolled patients is planned.

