### Outcome Measures

The primary outcomes include the improvement in homogeneity of pulmonary ventilation distribution after mobilization and optimal duration of early mobilization. Secondary outcomes include optimal duration of early mobilization for different surgical methods; correlation between bed rest time and optimal duration of early mobilization; and correlation between blood oxygen saturation, oxygenation index, and improvement in homogeneity of pulmonary ventilation distribution.

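### The analysis section lists only between-group tests for means and medians, although the primary comparison is the same patients at T0 to T5, and it does not clearly assign the one suitable method, mixed models, to that comparison.

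*Protocol article*

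**What the plan says.** The Study Design section describes a single cohort with no comparator. Under Procedure, "The following baseline parameters will be recorded when the patient is in decubitus position" (T0), and the Abstract adds that "These data will be recorded again at 15, 30, 60, 90, and 120 min after mobilization". Each patient therefore contributes up to six recordings. The Abstract gives the comparison of interest: "the changes in vital signs and ROI 1-4 values at each time point before and after mobilization will be compared". Under Outcome Measures, "The primary outcomes include the improvement in homogeneity of pulmonary ventilation distribution after mobilization and optimal duration of early mobilization".

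For the tests, the Statistical Analysis section states: "Means or medians will be compared between groups using the *t*-test, the Mann-Whitney *U*-test, and one-way analysis of variance". The sentence goes on to the F and Kruskal-Wallis tests and ends with a qualifier that each is used where appropriate. Two sentences later comes "Intention-to-treat analyses will be carried out using mixed models". No outcome, time effect or patient effect is attached to those models.

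One stated aim does compare distinct patients: "Secondary outcomes include optimal duration of early mobilization for different surgical methods".

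**The concern.** The first primary outcome is a change within the same patients. Mann-Whitney, one-way analysis of variance and Kruskal-Wallis are independent-sample tests by definition. The t-test is not described as paired, and its sentence speaks of groups. No paired t-test, signed-rank test, Friedman test or repeated-measures analysis of variance is named. An analyst who looks in this list for a way to compare six time points would most naturally take one-way analysis of variance or Kruskal-Wallis.

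Those tests leave the between-patient variance in the error term, and a within-patient comparison removes it. With positive correlation between a patient's recordings, a real change is then harder to detect. The choice between the list and the mixed model is also left open, so it could be made after the data are seen.

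**Working it through.** **The plan's own figure.** The Statistical Analysis section takes a minimum of 10 subjects (two-sided alpha 0.05, power 80%) from a prior study and plans 50. The 10 cannot be reproduced, because no effect size, SD or test is given. Solved backwards:

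- Paired, normal approximation: (1.960 + 0.842)/sqrt(10) = 0.89 SD of the differences.
- Paired, t distribution: about 1.00.
- 10 per group, unpaired: about 1.32.

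The article does not say which applies, so its sample-size statement does not show which test is intended.

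**Inputs.** n = 50 patients, 6 times and alpha 0.05 two-sided come from the article. The within-patient correlation rho is not given. It is assumed to lie between 0 and 0.8, with equal variances and the same correlation between all pairs of times. The shift of 0.4 SD is illustrative; with 50 patients, the paired effect detectable at 80% power is 0.404 SD of the differences.

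**Standard error of a before/after difference** (sigma = SD at one time):

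- Unpaired: sigma × sqrt(2/n) = sigma × sqrt(2/50) = 0.20 sigma, whatever rho is.
- Paired: sigma × sqrt(2(1 - rho)/n). At rho = 0.5 this is sigma × sqrt(1/50) = 0.141 sigma.
- Ratio: 1/sqrt(1 - rho). At rho = 0.5 this is 0.20/0.141 = 1.41.

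**Type I error and power**, by simulation (20,000 runs, n = 50, 6 times; t-tests on T0 against T1, analysis of variance over all six times):

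| rho | SE ratio | True alpha, unpaired t | True alpha, one-way ANOVA | Power at 0.4 SD, unpaired / paired |
|---|---|---|---|---|
| 0 | 1.00 | 0.050 | 0.049 | 0.50 / 0.49 |
| 0.3 | 1.20 | 0.019 | 0.008 | 0.51 / 0.65 |
| 0.5 | 1.41 | 0.006 | 0.0008 | 0.51 / 0.79 |
| 0.7 | 1.83 | 0.0006 | <0.0001 | 0.52 / 0.95 |
| 0.8 | 2.24 | <0.0001 | <0.0001 | 0.52 / 0.99 |

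The paired t-test and the repeated-measures analysis of variance held alpha between 0.048 and 0.052 throughout. A closed form agrees for the unpaired t-test. Its statistic has true SD sqrt(1 - rho), so at rho = 0.3 the true alpha is 2 × [1 - Phi(1.96/0.837)] = 2 × [1 - Phi(2.34)] = 0.019. Unpaired power stays near one half because the expected statistic is 0.4/0.20 = 2.0 against a critical value of about 1.98.

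**Sensitivity to the effect size.** Suppose the 10 subjects mean a paired effect of 1.00. At rho = 0.8 the raw shift is 1.00 × sqrt(2 × 0.2) = 0.632 SD, and the expected unpaired statistic is 0.632/0.20 = 3.16. Then (3.16 - 1.98)/sqrt(0.2) = 2.64, which is power of about 0.99 even with the wrong test. The loss matters for moderate effects, not for very large ones.

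**The case against.** The strongest reply is that the plan never assigns an independent-group test to the before/after comparison. The sentence is limited to groups and to appropriate use, the comparison of surgical methods is a genuine between-group aim, and t-test is not stated to be unpaired. The same section names mixed models, whose obvious use in one cohort measured six times is the repeated measurements. A poorly chosen label does not remove the method, and covariance structure and contrasts are details that an article may leave to a fuller document. Most of this stands. It rules out the stronger inference, which a reader might draw, that the error bars of the primary result will necessarily be wrong.

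It does not settle the point. The article chose to list its tests, and the list contains nothing explicitly suited to its primary question. The mixed model is tied to a population label that has no clear content here, and to no outcome.

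The size is also open to challenge: rho and the effect are assumptions, the loss nearly disappears for a very large effect, and the misuse is conservative, so under positive correlation it would not create a false claim of benefit. All of that is accepted.

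A reader might also infer that the planned Pearson or Spearman correlations would pool the repeated recordings and count each patient several times. The text does not support this. Bed rest time is one value per patient, and correlating it with optimal duration implies one value of that as well. The blood gases needed for the oxygenation index are listed only in the initial data collection. Oxygen saturation against homogeneity could be pooled, but nothing says that it will be.

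**Conclusion.** The point holds as a conditional defect in how the primary analysis is specified. The named tests for means and medians do not fit a comparison of the same patients at T0 to T5, and the method that fits is not clearly tied to it. If the between-group tests were used across times, standard errors would be 1.2 to 2.2 times too wide for rho between 0.3 and 0.8. One-way analysis of variance would run at a true alpha of about 0.008 at rho 0.3 and below 0.001 from rho 0.5. Power for a moderate shift would fall well below that of a paired analysis. These sizes rest on an assumed correlation, equal variances and an illustrative effect, none of which the article gives. If the mixed model is the intended primary analysis and models the within-patient correlation, the problem is one of wording only.

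**What to change.** In the Statistical Analysis section:

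1. State that the homogeneity index and the other T0 to T5 comparisons are analysed by a mixed model with time as a categorical fixed effect and within-patient correlation, with contrasts against T0. Paired tests are an acceptable alternative; in that case, say how the five contrasts are handled for multiplicity.
2. Restrict the t-test, Mann-Whitney, one-way analysis of variance and Kruskal-Wallis tests to comparisons between distinct patients, such as surgical methods, with one value per patient.
3. Replace the intention-to-treat label with a defined analysis set, for example all enrolled patients with a T0 recording.

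The cost is a few sentences. Mixed models are already in the plan, and no new data, visits or patients are needed. The change should be fixed before the data are analysed.

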### Definitions

Homogeneity index is defined as the ratio of EIT values of ventral to those of dorsal ROIs; thus, lower levels (~1.0) represent better homogeneity of ventilation (18).Optimal duration of early mobilization is defined as the mobilization time at which homogeneity index is closest to 1.Bed rest time is the time from the start of surgery to the time of first mobilization.

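### The saturation–homogeneity correlation is assigned Pearson or Spearman, which need one independent pair per patient, although both variables are recorded six times and the pair is not defined

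*Protocol article*

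**What the plan says.** Under Outcome Measures, one secondary outcome of the Protocol article is the "correlation between blood oxygen saturation, oxygenation index, and improvement in homogeneity of pulmonary ventilation distribution".

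Under Procedure, the T0 set includes "oxygen saturation (SO_2_), respiratory rate (RR), and EIT ROI 1-4". The same set is then "recorded at 15 min (T_1_), 30 min (T_2_), 60 min (T_3_), 90 min (T_4_), and 120 min (T_5". Saturation and the EIT regions are therefore read side by side six times in each patient. Under Definitions, "Homogeneity index is defined as the ratio of EIT values of ventral to those of dorsal ROIs", so the index can be computed at each of those six times. Improvement since T0 has up to five values per patient.

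The blood gases are different. Under Procedure, "arterial blood gas analysis (PH, PaO_2_, PaCO_2_, FiO_2" appears in the enrolment data and is not part of the repeated set.

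Under Statistical Analysis, correlations are covered by one sentence: "Pearson correlation or Spearman rank correlation coefficient will be used to assess the correlation between variables, as appropriate". The next sentence reads "Intention-to-treat analyses will be carried out using mixed models". It is not tied to any named outcome or to the correlations.

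**The concern.** The usual tests of a Pearson or Spearman coefficient treat each pair as an independent unit. Here the independent unit is the patient, and each patient has several linked pairs. The article gives no time point and no per-patient summary that would reduce them to one. That leaves two routes.

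- **Pooling the records.** This treats 250 or 300 readings from 50 patients as that many independent pairs and overstates significance.
- **One pair per patient.** This keeps the error rate, but compares patients with each other. The Background and Discussion are about how ventilation changes over the time spent mobilised, and on that question a between-patient coefficient is silent.

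The two routes estimate different things, and the article does not choose between them. The concern is limited to saturation. It does not extend to the comparison of means, or to an oxygenation index built from a single blood gas.

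**Working it through.** **Inputs from the Protocol article.** 50 patients; six joint readings (T0 to T5), hence five after baseline; two-sided 5% level. The article states no error rate or power for this correlation, so there is no figure of its own to reproduce. The 10-subject minimum it cites comes with no effect size or standard deviation and was not derived for this outcome.

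**Assumed input.** The within-patient (intraclass) correlation of each variable, ICCx and ICCy. The article gives neither, so a range is shown.

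**Step 1: pooling the raw records, no true association.** With m records per patient and exchangeable readings, the variance of the pooled coefficient is inflated by

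DE = 1 + (m − 1) × ICCx × ICCy,

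and the actual false-positive rate is 2 × [1 − Φ(1.96/√DE)].

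| m | ICC (both) | DE | Rate, formula | Rate, simulated Pearson / Spearman |
|---|---|---|---|---|
| 5 | 0.2 | 1.16 | 6.9% | 6.8% / 6.4% |
| 5 | 0.5 | 2.00 | 16.6% | 15.6% / 15.3% |
| 5 | 0.8 | 3.56 | 29.9% | 29.4% / 28.9% |
| 6 | 0.2 | 1.20 | 7.4% | 6.9% / 7.0% |
| 6 | 0.5 | 2.25 | 19.1% | 18.2% / 17.8% |
| 6 | 0.8 | 4.20 | 33.9% | 34.8% / 33.3% |

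The simulations used 50 patients and 6,000 trials per row. If either ICC is 0, DE = 1 and the rate is 5%.

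**Step 2: pooling changes from T0, which is closer to the stated outcome.** Under the same exchangeable model, a change from T0 has variance 2(1 − ICC)σ². Two changes in one patient share the T0 reading and have covariance (1 − ICC)σ². Their correlation is therefore 0.5 whatever the ICC. For saturation level against change in homogeneity, DE = 1 + 4 × ICCx × 0.5:

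- ICCx 0.2: DE = 1.4, rate 9.8% (simulated 9.5%)
- ICCx 0.5: DE = 2.0, rate 16.6% (simulated 16.7%)
- ICCx 0.8: DE = 2.6, rate 22.4% (simulated 22.1%)

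**Step 3: one pair per patient.** With a single time or a patient mean, the simulated false-positive rate was 4.5% to 5.5% in every setting. With 50 pairs, power by Fisher's z (standard error 1/√47) is about 28% for a true between-patient correlation of 0.2 and about 56% for 0.3. It reaches 80% at about 0.39.

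**Step 4: does a simple within-patient analysis solve it?** Not automatically. Readings are 15 to 30 minutes apart, so residuals may be serially correlated. A test on patient- and time-centred values (50 patients, six times, 244 degrees of freedom, no true link), which makes the same independence assumption as a random-intercept model, was simulated with AR(1) errors in both variables. It rejected in about 5% of trials at lag-1 correlation 0, and in about 8%, 12% and 14% at assumed values of 0.5, 0.7 and 0.8. The residual covariance therefore has to be part of the fix.

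**The case against.** The strongest reply is that nothing in the plan is invalid. It says coefficients will be chosen as appropriate and never says that records will be pooled. A competent analyst would take one value per patient and hold 5%, and a condensed article may leave the choice of that value to a fuller document. A between-patient question is also a natural reading of the outcome. It is the only possible reading for the oxygenation index, whose blood gases are listed once. Mixed models are already named.

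Much of this stands, and it rules out three stronger readings.

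- **That the planned test runs at an inflated error rate.** The documents do not support this. The inflation depends on pooling, which is not stated, and on ICCs that are not given.
- **That one pair per patient must discard most of the data.** It need not: a patient mean, a slope or the change at a named time is one valid pair, and a mean or slope draws on all the readings.
- **That a between-patient coefficient may have the wrong sign.** It estimates a different quantity. Opposite signs would need an assumed scenario for which the article offers no basis.

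What does not stand is that the text already resolves the matter. The point does not rest on omitted detail. The article fixes repeated joint readings and names, for correlations, only a method that cannot use them as repeated readings. The mixed-model sentence is confined to intention-to-treat analyses.

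**Conclusion.** The concern holds in a limited form. For saturation against improvement in homogeneity, the named method fits the recorded data badly and the pair is undefined. The consequence depends on the route taken.

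- **If raw records were pooled:** about 7% to 34% false positives at nominal 5%, assuming exchangeable readings and ICCs of 0.2 to 0.8 in both variables. For saturation level against change from T0, the range is about 10% to 22%.
- **If one pair per patient is used:** about 5%, but with only a between-patient answer.

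This affects one part of a secondary outcome and leaves the primary outcomes untouched. It should be corrected because the better method is cheap and already within the plan.

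**What to change.** In Statistical Analysis:

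1. State that repeated records will not be pooled in Pearson or Spearman tests.
2. For saturation, model change in the homogeneity measure from T0 at T1 to T5 with a mixed model. State whether that measure is the index itself or its distance from 1. Include time as a factor and saturation split into the patient's mean and the deviation from that mean.
3. Account for the patient and for serial correlation. Use either a random patient intercept with an AR-type residual, or an unstructured covariance over the five times. An unstructured covariance already carries the patient effect, so it should not be combined with a random intercept.
4. Report the within-patient coefficient with its 95% CI. The coefficient for the patient mean gives the between-patient answer from the same model.
5. Keep Pearson or Spearman for pairs with one value per patient. This includes the oxygenation index (assumed to come from the once-listed blood gas) against one named homogeneity-improvement value per patient.

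The cost is a few sentences, one extra model and a slightly more complex report for a secondary outcome. No new data are needed.

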### Ethics and Dissemination

The study protocol has been approved by the Institutional Review Board of Dong E Hospital Affiliated to Shandong First Medical University (2020036). The trial is registered at chictr.org.cn with identifier ChiCTR2100042877, registered on January 31, 2021. The results of the study will be presented at relevant national and international conferences and submitted to international peer-reviewed journals. There are no plans to communicate results specifically to participants. Important protocol modifications, such as changes to eligibility criteria, outcomes, or analyses, will be communicated to all relevant parties (including investigators, IRBs, trial participants, trial registries, journals, and regulators) as needed via email or in-person communication.

